
**Fig. 2 Fig2:**
[figure not shown]
Twelve-week aerobic exercise training program [37]. Note: heart rate reserve (HRR) = % of target intensity (HR_max_ − HR_rest_) + HR_rest_

To achieve a total of 150 min of light-to-moderate or moderate-to-vigorous activity each week, participants will be asked to engage in additional home-based aerobic activities (e.g., walking). Participants will be asked to keep an activity diary including a record of their resting heart rate, type of exercise performed, duration of the exercise, and maximum heart rate during all supervised and home-based exercise sessions.

### Strategies to enhance participant recruitment, adherence, and retention

Efforts to optimize participant engagement will include on-site, face-to-face recruitment and physician endorsement. Several strategies to improve participant adherence and retention will be also be employed including group-based, individually tailored exercise training sessions; personalized performance feedback (e.g., weekly activity diary review); follow-up phone calls to inquire about missed sessions; ability to make-up missed session(s) over the course of the 12-week intervention; and scheduling flexibility.

### Primary outcomes

#### Participant accrual, adherence, retention, and safety

The primary feasibility outcome measures for this study will include variables associated with participant recruitment, adherence, retention, and safety. Recruitment rate will be calculated by the number of patients who consent to participate divided by the number of deemed eligible to participate by their primary care oncologist/hematologist. Program adherence will be calculated by counting the actual number of sessions that the participant engaged in divided by the recommended number of weekly sessions. Participants will also be asked to record their activity duration (time) and intensity (as measured by heart rate) following each training session in order to calculate exercise volume. Participant retention will be determined by reporting the number of participants who complete baseline and post-intervention testing. Program safety will be assessed by weekly tracking and monitoring the number of adverse events or injuries that occur during the duration of the study. An investigators meeting will be held every 3 months to review and discuss all reported minor adverse events (e.g., muscle stiffness, activity-related fatigue) and injuries (e.g., muscle strain) for early risk identification and modification of study procedures as needed. All serious adverse events will be immediately disseminated to all study investigators for review and reported to the Nova Scotia Health Authority Research Ethics Board. There are currently no stopping guidelines for this trial.

### Secondary outcomes

Baseline demographics (age, sex, ethnicity, education, employment status, family income), lifestyle behaviors (general health, aerobic fitness, physical activity behaviors, sleep habits, tobacco use, and alcohol consumption), and medical history (cancer diagnosis, cancer treatment(s) received, comorbid health conditions, markers of cardiac risk [43]) will be collected by a combination of self-report and participant-consented medical record review.

#### Cardiac function

Resting baseline and post intervention LVEF will be performed on all participants with a multigated acquisition (MUGA) scan. MUGA is a non-invasive, cost-effective, and reliable measure of heart function by tracking blood flow through the ventricles. Serial monitoring will permit for the early detection of decreased left ventricular function [44].

#### Cardiorespiratory fitness

CPETs will be performed to determine peak aerobic capacity (VO_2_ peak) that the participant reaches in the absence of any clinical symptoms (e.g., fatigue, leg pain, changes in ECG). The CPETs will be performed in accordance with the American Heart Association (AHA) guidelines [42]. In brief, all participants will complete either the BRUCE treadmill protocol or a RAMP treadmill protocol [42]. A standard 12-lead ECG will be recorded concurrently with the CPET [42]. Resting ECG and post-exercise ECG will also be recorded. Blood pressure will be recorded manually at rest prior to the test, during the CPET (at the end of every exercise stage), and during recovery [40]. All tests will be performed by a CPET technician and supervised by a cardiologist. Upon completion, all CPET results will be reviewed by a cardiologist to determine if there is any evidence of undiagnosed pre-existing cardiovascular disease or any contraindications to participating in the study exercise protocol.

In general, maximal symptom-limited exercise testing (CPET) is a reasonably safe procedure [45]. The American Thoracic Society/American College of Chest Physicians report that the number of life-threatening complications or deaths was approximately 2 to 5 per 100,000 tests [45]. Statistics, based on a review of the literature, published by the AHA report the number of sudden cardiac deaths which ranges from 0 to 5 per 100,000 tests [46]. Similarly, systematic reviews suggest that CPET is safe for cancer patients. For example, a review of oncology studies that utilized exercise testing reports that adverse events were reported in less than 15 % of the studies and that there were no reports of death [47]. Another systematic review reported that adverse events occurred in only 1 % of oncology patients that performed exercise testing [48]. Together, the evidence clearly indicates that CPETs can be safely administered to individuals receiving and/or recovering from cancer treatment.

#### Cardiac biomarkers

Blood samples will be collected from the participants prior to and immediately following the 12-week exercise intervention to determine the participant’s lipid profile and fasting glucose. Markers of cardiac injury including high-sensitivity troponin (hs-TNT), N-terminal pro-brain natriuretic peptide (NTproBNP), and C-reactive protein (CRP) levels as well as various systemic markers of inflammation will also be collected. These tests will occur within 7 days of starting and ending the program. Samples will be processed at the QEII HSC to quantify levels of lipids, fasting glucose, hs-TNT, NTproBNP, and CRP. Serum also will be extracted from the blood samples in order to quantify markers of systemic inflammation (cytokines). A BioPlex Pro human cytokine immunoassay will be used to quantify the levels of 27 different cytokines (e.g., IL-1α, IL-1β, IL-4, IL-6, IL-10, IL-17, TNFα). Assays will be performed as per manufacturer’s instructions. A MAGPIX Suspension Array System will be used to analyze the cytokine assay. All serum samples will be stored at −80 °C until they are required for analysis. With participant consent, blood samples will be stored for use for future related studies.

#### Total physical activity

To capture additional activity behaviors, total physical activity across four life domains (i.e., job-related, house and yard work, recreation, and active transportation) will be assessed using the long version of the International Physical Activity Questionnaire (IPAQ) pre- and post-intervention. Physical activity levels as well as continuous values of MET-minutes per week (MET = metabolic equivalent of task) will be calculated according to the IPAQ scoring protocol [49, 50].

Self-reported time spent sitting (sedentary behaviors) will also be assessed by the IPAQ by calculating the sum of the time spent sitting (e.g., at a desk, watching television, reading, and time spent sitting in a vehicle for the purpose of transportation). Time spent sitting will be calculated according to the IPAQ scoring protocol [50]. The IPAQ tool has demonstrated acceptable reliability and validity in adults 18–65 years of age and is comparable to other self-reported measures of physical activity [49].

#### Anthropometrics

Body weight will be assessed to the nearest 0.1 kg, and height will be measured to the nearest 0.1 cm using a Tanita body composition analyzer. Body mass index will be calculated as the weight in kilograms divided by the height in meters squared (kg/m^2^). Waist girth measurements will be taken clear of participant clothing at the top of the iliac crest to the nearest 0.1 cm [41].

#### Patient-reported outcomes

Cancer-related fatigue and disease-specific quality of life will be assessed pre- and post-intervention using cancer-specific, self-administered Functional Assessment of Cancer Therapy (FACT) tools [51–55]. The FACT tools are reliable and valid measures of disease-specific quality of life and fatigue [51–55].

### Sample size

For this feasibility study, we will aim to recruit 20 breast and hematological cancer patients over a course of 12 months. Preliminary data will inform power analyses for a larger randomized trial. Likewise, the number of patients that we are able to recruit during this period will determine the number of collaborating centers needed to obtain sufficient participant recruitment for future studies.

### Ethical governance and dissemination

This study has received ethical approval from the Nova Scotia Health Authority Research Ethics Board (REB file: NSHA ROMEO File #: 1019999). Any protocol amendments will be submitted for further review and approval. Study findings will be presented at conferences and submitted for publication in peer-reviewed journals. Only those team members who fulfill authorship criteria will be included as authors on any future publications. Professional writers will not be employed.

### Confidentiality and access to data

All study personnel will be trained in the requirement of participants’ confidentiality according to the Tri-Council Policy Statement: Ethical Conduct for Research Involving Humans. Participant identification numbers will be assigned upon study enrollment, and access to personally identifiable information will be limited to members of the research team. All data files will be stored on a password-protected computer in a secure research laboratory.

#### Data management and analysis

De-identified data will be double entered in SPSS version 22, and basic descriptive statistics will be conducted to describe the study sample and outcomes. Rates for process measures (e.g., recruitment, adherence) will be reported. Exploratory correlational analyses will also be conducted to examine the relationship between program adherence and secondary outcome measures. Reasons for non-participation and attrition will be recorded to inform future recruitment and retention strategies. Program safety will be determined by examining the total number adverse events that occur over the duration of the 12-week exercise program. The total number of adverse events over the course of the study will be divided by the total number of participant hours to determine the number of adverse events per participant hour. Secondary outcome measures will be assessed at baseline (week 0) and post-intervention (week 13) using descriptive statistics and 95 % confidence interval estimation. Change between time points will also be assessed in this way, and within-group correlations will be calculated between the two time points. The data will be used to determine the most appropriate outcome measure for the main study and in sample size calculations required for a future grant submission. Descriptive statistics and confidence intervals will also be used to examine the trends in the biomarker data. This information will be used to determine which markers to focus on in future grant submissions. Should we find that the biomarker data is normally distributed, then a 95 % confidence interval for paired normally distributed data will be used; otherwise, a non-parametric approach will be taken.

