The specific objectives of the study are as follows: (1) to examine feasibility outcomes (e.g., recruitment, program adherence, and safety) and (2) to explore the effects of the exercise program on biological markers of AC-mediated cardiotoxicity (e.g., levels of inflammation) as well as patient-centered outcomes (e.g., increased aerobic capacity, quality of life). We hypothesize that an individualized AET program for cancer patients receiving active AC-based treatment will be both safe and feasible with an anticipated adherence of 66–85 % [37]. We further hypothesize that the AET program will result in improvements in the overall levels of physical activity, aerobic fitness, and quality of life. Given the dearth of knowledge surrounding both the measurement of cardiac biomarkers and the cardioprotective nature of aerobic exercise in human models, no a priori hypotheses have been made. Instead, this study will serve to inform future iterations.

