## Methods/design

### Study design and procedures

The protocol was drafted in accordance with the SPIRIT 2013 statement [38]. This is a single-arm, prospective (pre-post) feasibility study of a supervised 12-week light-to-moderate to moderate-to-vigorous intensity AET program. The study flow is presented for each separate cancer site in Fig. 1. Potential participants will be identified and screened for preliminary eligibility by their medical oncologist/hematologist during a regular office visit at the Queen Elizabeth II Health Sciences Center (QEII HSC) in Halifax, Nova Scotia, Canada. Pending preliminary screening for study eligibility and medical approval to participate, potential participants will be approached by a member of the medical staff to seek permission to refer them to the research coordinator to discuss the details of the study. Pending approval to be contacted by the research team, eligible participants will be provided with a detailed review of the study and informed consent will be sought by the research coordinator. Eligible participants who provide informed consent will undergo additional cardiovascular risk and fitness assessment (i.e., cardiopulmonary exercise test (CPET)) to determine study suitability and ability to safely participate in a low-to-moderate or moderate-to-vigorous aerobic training program. Those meeting the study criteria will then complete a pre-exercise baseline assessment (week 0) of anthropometric measures, select cardiac biomarkers, lifestyle behaviors, and quality of life. Based on the findings of the exercise stress test and baseline assessments, an individualized, bi-weekly AET program will be developed (weeks 1–12). Pending the completion of the 12-week training program, participants will repeat the exercise stress and cardiac function tests and the assessments measured at baseline (week 13). The study is registered with ClinicalTrails.gov (NCT02471053).

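### The planned correlation of adherence with secondary outcomes should name the outcome quantity and adjust for its week-0 value

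*Protocol article*

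**What the plan says.** The analysis is given in one sentence of the protocol article, under Data management and analysis: "Exploratory correlational analyses will also be conducted to examine the relationship between program adherence and secondary outcome measures". No type of correlation, form of outcome or covariate follows.

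Adherence is defined under the primary outcomes: "Program adherence will be calculated by counting the actual number of sessions that the participant engaged in divided by the recommended number of weekly sessions". It is therefore something the patient does after baseline, not something assigned.

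The same analysis section shows that the material for an adjusted analysis will exist: "Secondary outcome measures will be assessed at baseline (week 0) and post-intervention (week 13) using descriptive statistics and 95 % confidence interval estimation". It also plans a change analysis, but does not link it to adherence: "Change between time points will also be assessed in this way, and within-group correlations will be calculated between the two time points".

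On design, the article states: "This is a single-arm, prospective (pre-post) feasibility study". On size: "we will aim to recruit 20 breast and hematological cancer patients over a course of 12 months".

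**The concern.** With no control group, the adherence correlations are the only planned analysis that relates differences in exercise exposure between patients to differences in outcome. Exposure here is attendance, and attendance may depend on how well the patient was at entry. A patient with better fitness or quality of life at week 0 may come to more sessions and also score better at week 13, whether or not the sessions did anything.

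The two plain readings of the sentence fail in opposite directions. Correlating adherence with the week-13 value carries the baseline difference forward and can suggest benefit where there is none. Correlating adherence with the change picks up regression to the mean and can suggest harm or hide a benefit. Because the sentence leaves the outcome quantity open, the direction of any artefact would depend on a choice made later by the analyst.

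What is at stake is how an exploratory result is read, not the feasibility conclusions.

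**Working it through.** **Figure to reproduce.** None. The article gives no correlation, effect size or power for this analysis, and the target of 20 has no power calculation behind it. The check is therefore of the mechanism and its possible size.

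**Inputs from the article.** One arm; n = 20; outcomes at week 0 and week 13; adherence as sessions attended over sessions recommended.

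**Assumed inputs (not in the documents).**
- a = correlation of adherence with the week-0 value, 0.2 to 0.5.
- r = correlation of the week-0 with the week-13 value, 0.5 to 0.9.
- Equal standard deviations at both visits, set to 1, with the outcome scored so that higher is better.
- No effect of exercise: given the week-0 value, adherence and the week-13 value are unrelated.

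**Formulas.**
- Adherence with week-13 value: a × r.
- Adherence with change: the covariance is a·r - a = -a(1 - r) and the SD of change is √(2(1 - r)), so the correlation is -a × √((1 - r)/2).
- Adherence with week-13 value, adjusted for week 0: (a·r - a·r)/√((1 - a²)(1 - r²)) = 0.

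**Results.**

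| a | r | Week-13 value | Change | Adjusted |
|---|---|---|---|---|
| 0.2 | 0.5 | +0.10 | -0.10 | 0 |
| 0.2 | 0.9 | +0.18 | -0.04 | 0 |
| 0.3 | 0.7 | +0.21 | -0.12 | 0 |
| 0.4 | 0.7 | +0.28 | -0.15 | 0 |
| 0.5 | 0.5 | +0.25 | -0.25 | 0 |
| 0.5 | 0.9 | +0.45 | -0.11 | 0 |

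Over the whole grid the week-13 bias runs from +0.10 to +0.45. The change bias runs from about -0.05 (0.2 × √0.05 = 0.045) to -0.25 (0.5 × √0.25). If a = 0, all three are zero.

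A simulation of 1,000,000 draws per scenario, over a = 0, 0.2, 0.3 and 0.5 and r = 0.5, 0.7, 0.8 and 0.9, agreed with the formulas to within about 0.002. The adjusted values lay between -0.002 and 0.002.

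**What this means at n = 20.** The same draws, cut into 50,000 samples of 20, give the chance of a positive correlation with two-sided p < 0.05 when week-13 values are used unadjusted. It is 6 % at a = 0.2, r = 0.5; 14 % at a = 0.3, r = 0.7; and 54 % at a = 0.5, r = 0.9. It should be 2.5 %.

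**Precision.** By Fisher's z, the half-width on the z scale is 1.96/√17 = 0.475. An observed 0.21 has a 95 % interval of -0.26 to 0.60, an observed 0.28 has -0.19 to 0.64, and an observed 0 has ±0.44. With one covariate the half-width becomes 1.96/√16 = 0.49, or ±0.45 around zero.

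**The case against.** The strongest reply is that this reads a great deal into one sentence of a condensed article. Covariates and outcome form for an exploratory correlation are commonly left to the full protocol or analysis plan, neither of which is shown, and a correlational analysis could include a partial correlation. That is fair, and the silence by itself is no error. What stands is that the one method named, taken plainly, has a better alternative that needs no new data.

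Three stronger readings are tempting, and the document does not support them.

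- A reader might infer that fitter patients' better attendance *will* look like a dose-response. That needs the week-13 value as the outcome and a positive link between baseline status and attendance. The article states neither, and with change scores the artefact has the opposite sign. It also makes no dose-response claim and labels the analysis exploratory.
- A reader might infer that these correlations choose the outcome for the main trial. The sentence on that use, "The data will be used to determine the most appropriate outcome measure for the main study and in sample size calculations", directly follows the sentences on pre-post summaries, intervals and change. The adherence sentence stands earlier, beside the process measures, and no decision rule is attached to it.
- A reader might infer that baseline adjustment makes the association causal. It removes only confounding by that outcome's own week-0 value. Toxicity during chemotherapy can still cause both missed sessions and poorer outcomes.

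It is also true that at n = 20 the intervals are wide with or without adjustment. That limits what can be learned, but it is no reason to prefer the biased estimate.

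**Conclusion.** The point holds as a minor, no-cost improvement. The article plans an exploratory correlation without fixing whether level or change is used and without naming baseline adjustment. Either plain choice is biased if attendance depends on baseline status: by +0.10 to +0.45 or by -0.05 to -0.25, under the assumed ranges for a and r, equal standard deviations and no exercise effect. The size rests wholly on those assumptions, and it vanishes if attendance and baseline are unrelated. Recruitment, adherence, retention and safety, which are the primary outcomes, are not affected.

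**What to change.** Replace the sentence with a specified analysis. For each secondary outcome measured at both visits, estimate the association between adherence and the week-13 value adjusted for the week-0 value of the same outcome, by partial correlation or linear regression, and report it with a 95 % confidence interval. Add that the result is exploratory and is not evidence of a dose-response, since toxicity during treatment may affect both attendance and outcome.

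Cost: a change of wording and one degree of freedom per model. The week-0 values are already collected, and no visit, measurement or patient is added.

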**Methods/design:**

This is a prospective, single-arm (pre-post-test design), feasibility study of a supervised 12-week progressive, light-to-moderate to moderate-to-vigorous intensity AET program for patients (18–65 years) receiving AC chemotherapeutic treatment for a primary/non-recurrent breast cancer or hematological malignancy. Both feasibility (e.g., participant recruitment, program adherence, safety) and intervention outcome (e.g., biological markers of cardiotoxicity, aerobic capacity, quality of life) measures will be collected. The AET program will include two, 45-min community-based exercise sessions (treadmill or cycle) per week for a total of 12 weeks. All exercise sessions will be supervised by trained exercise specialists.

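### Program safety, a primary outcome, is determined from a pooled adverse-event total and hourly rate that, for any given total, show neither how many events were serious nor how many participants were affected

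*Protocol article*

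**What the plan says.** In the protocol article, the section *Participant accrual, adherence, retention, and safety* places safety among the primary feasibility outcomes and measures it by counting events: "Program safety will be assessed by weekly tracking and monitoring the number of adverse events or injuries". The end of the *Background* hypothesises that the program will prove safe as well as feasible.

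*Data management and analysis* then names two safety statistics:

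- a total: "Program safety will be determined by examining the total number adverse events that occur over the duration of the 12-week exercise program";
- a rate: "The total number of adverse events over the course of the study will be divided by the total number of participant hours".

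That section gives no split by seriousness and no count of participants with an event. It does contain a general sentence that "basic descriptive statistics will be conducted to describe the study sample and outcomes".

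The outcomes section distinguishes classes of event, but for oversight. Minor events (muscle stiffness and activity-related fatigue are the examples) and injuries (muscle strain) go to a three-monthly investigators' meeting. For the rest, "All serious adverse events will be immediately disseminated to all study investigators for review", with a report to the ethics board. The article says there are currently no stopping guidelines.

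**The concern.** A total weights every event equally. One serious cardiac event and one report of muscle stiffness each add one to the count, and each adds the same amount to the hourly rate. Several events in one participant are also indistinguishable from one event in each of several participants. A benign profile and a worrying one can therefore give the same two numbers.

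This matters because participants exercise, at up to 85% of heart rate reserve, while receiving drugs that the article itself describes as cardiotoxic. A reader of the results will want to know how many people had an event and how many events were serious. The *Discussion* says the findings will inform the safety of future trials, and *Sample size* names a larger randomized trial as the next step. A pooled figure carries little of that information forward.

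**Working it through.** The article states no expected event count, safety rate or threshold, so there is no figure to reproduce. The check is whether the two named statistics can tell different safety profiles apart.

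**Inputs.** Planned participants n = 20 (*Sample size*). Statistics: the total E and the rate E/H, where H is total participant hours (*Data management and analysis*). The event counts below are assumptions for illustration. H needs no value, because it is the same for both profiles in each comparison.

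**Formula for participants affected.** With x of n participants having at least one event, the exact (Clopper-Pearson) 95% interval is:

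- lower limit: the 2.5% point of Beta(x, n − x + 1), or 0 if x = 0;
- upper limit: the 97.5% point of Beta(x + 1, n − x). For x = 0 this equals 1 − 0.025^(1/20) = 0.168.

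**Comparison 1, seriousness (assumed E = 36).**

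| | Profile A | Profile B |
|---|---|---|
| Minor events | 36 | 33 |
| Serious events | 0 | 3, in 3 participants |
| Total E | 36 | 36 |
| Rate | 36/H | 36/H |
| Participants with a serious event | 0/20 = 0% | 3/20 = 15% |
| Exact 95% CI | 0 to 16.8% | 3.2 to 37.9% |

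The first two summary rows (total and rate) are what the plan names, and they are identical. The last two are not in the plan, and they differ.

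**Comparison 2, clustering (assumed E = 12).**

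| | All in one participant | One in each of 12 participants |
|---|---|---|
| Total E | 12 | 12 |
| Rate | 12/H | 12/H |
| Participants affected | 1/20 = 5% | 12/20 = 60% |
| Exact 95% CI | 0.1 to 24.9% | 36.1 to 80.9% |

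Again the named statistics agree and the profiles do not.

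**Dependence on the assumed counts.** The identity does not rest on 36 or 12. E is a sum over all events, so it stays the same when events are reclassified by seriousness or reallocated among participants, and E/H stays the same with it.

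**The case against.** The strongest reply is that this is a condensed article. Tables by seriousness and by participant are ordinary content of a full protocol or analysis plan, nothing in the section excludes them, and the sentence on basic descriptive statistics would cover them. That would settle the matter if the article were silent. It is not silent: it says by what safety will be determined. The general sentence permits a breakdown but does not replace that rule.

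Other parts of the reply stand and limit the point:

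- The examples hold the total fixed. A reader might infer that the statistics do not respond to serious events at all. They do: an additional serious event raises both. They cannot show that the added event was serious.
- A reader might infer that serious events would be hidden. The article does not support this: each one is circulated at once to all investigators and reported to the ethics board.
- A reader might see a contradiction with the outcomes section. There is none: its classes set review routes and were not declared as analysis categories.
- No threshold, test or stopping rule is tied to the safety statistics, so no planned decision would change.
- It would be tempting to ask that the conclusion rest mainly on serious events and injuries. In a single-arm study during chemotherapy, treatment itself causes events, so that weighting is debatable and is not proposed here.
- How participant hours are to be counted is a separate question of definition. This point does not depend on it.

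**Conclusion.** The point holds in limited form and is worth correcting. For any given total, the two statistics by which the article determines a primary outcome cannot show how many events were serious or how many participants were affected. With an assumed 36 events, the same total and rate are compatible with 0/20 or 3/20 participants having a serious event. With an assumed 12 events, they are compatible with 1/20 or 12/20 participants affected. The event counts are illustrative, and the denominator is the planned 20.

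The 0/20 and 3/20 intervals overlap, so separate reporting would not support a formal comparison at this sample size. The benefit is a safety summary that can be interpreted. The documents do not support a claim that serious events go unreported, that the article contradicts itself, or that a go/no-go decision is affected.

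**What to change.** In *Data management and analysis*, replace the rule that safety is determined from the total with the following:

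1. Report serious and non-serious adverse events separately, with injuries shown within each. For each, give the number of events, and the number and proportion of participants with at least one, with an exact 95% confidence interval for the proportion.
2. List each serious or cardiovascular event individually.
3. Keep the pooled total and the rate per participant hour as supporting description.

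**Cost.** A few sentences and a small table. The oversight procedures already separate serious events from minor events and injuries, so the information should be at hand. The article gives examples of these classes rather than definitions, and an injury can be serious, so a short definition of each should accompany the table. The main downside is sparse counts with wide intervals: one affected participant in 20 is 5%, with an interval of 0.1 to 24.9%.
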